# Corindus Randomised Controlled Trial Summary

| **Title:** | Percutaneous Coronary Intervention using assisted robotic technology: a randomised controlled trial |
| --- | --- |
|  |  |
| **Short Title:** | **P**CI using **A**ssisted **R**obotic **T**echnolog**Y** trial: the **PARTY** trial |
|  |  |
| **Study Description:** | Coronary artery disease is a leading cause of death globally, nationally and locally. Currently in South Western Sydney Local Health District Interventional Cardiologists perform Percutaneous Coronary intervention (PCI) procedure which opens coronary arteries that are narrowed or blocked by the build-up of atherosclerotic plaque. PCI may also be used to relieve symptoms of coronary heart disease or to reduce heart damage during or after a heart attack.  With new technology, engineering and training development, a technology-assisted percutaneous coronary intervention (PCI) device has the potential to increase procedural accuracy, reduce radiation exposure to participants and staff, improved ergonomics, and reduce major adverse cardiac events. To date we are not aware of any randomised controlled trial data supporting this technology |
| **Study Design:** | This is a randomized controlled trial of the CorPath GRX System versus standard PCI to compare participant outcomes at 72 hours post-procedure or hospital discharge, day 30 and 1 year. |
|  |  |
| **Study Objective:** | This study will assess the safety, effectiveness including the clinical and technical performance and cost analysis of technology-assisted PCI versus standard PCI performed by a cardiologist in a randomised controlled trial. |
| **Effectiveness Performance Measures:** | **Clinical Success:**  Less than 30% residual stenosis (visual estimate) post PCI, without in-hospital major adverse coronary events (MACE).  **Technical Success:**  Defined as successful completion of the PCI absent ***unplanned*** conversion to manual operation of guidewires or balloon/stent catheter or inability to navigate vessel anatomy or poor guide catheter support. |
|  |  |
| **Safety Measures:** | **Major Adverse Cardiac Event (MACE):**  MACE that occurs within 72 hours of the procedure or prior to hospital discharge, whichever occurs first, day 30 and 1 year  **Serious Adverse Events:**  All Serious Adverse Events (SAEs) from the start of the PCI procedure until the end of the study will be summarized. |
| **Cost Measures:** | Total procedural cost of PCI at day 30 and 1 year |

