### Major Adverse Cardiac Events (MACE)

MACE will be measured at each visit of the study.

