## **Lost to follow up**

A participant will be considered lost to follow-up if he or she fails to return for scheduled visits and is unable to be contacted by the study site staff.

The following actions must be taken if a participant fails to return to the clinic for a required study visit:

- The site will review the Electronic Medical Records (EMR) and/or contact the referring Cardiologist to determine if the participant is alive.
- The site will attempt to contact the participant and reschedule the missed visit ( within 1 month) and counsel the participant on the importance of maintaining the assigned visit schedule and ascertain if the participant wishes to and/or should continue in the study.
- Before a participant is deemed lost to follow-up, the investigator or designee will make every effort to regain contact with the participant (where possible, 3 telephone calls and, if necessary, a certified letter to the participant’s last known mailing address or local equivalent methods). These contact attempts should be documented in the participant’s medical record or study file.
- Should the participant continue to be unreachable, he or she will be considered to have withdrawn from the study with a primary reason of lost to follow-up.

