### Event Assessments

This study is not using any unregistered products therefore only serious adverse events that meet the MACE definition will be reported from visit 2 until the end of study visit (visit 5). Event Assessments will be reviewed by the End-Point Adjudication Committee.

**Major Adverse Cardiac Event (MACE):** MACE is defined as cardiac death, Q-wave or non Q-wave myocardial infarction (MI), or clinically driven target vessel revascularization (TVR) by percutaneous or surgical methods.

**Cardiac Death:** Death due to cardiac causes. If the cause of death cannot be determined, it will be categorized as cardiac.

Myocardial Infarction (Protocol Definition):

Clinically relevant MI after coronary revascularization will be defined by the 4^th^ Universal Definition of PCI related MI. Events as defined by the Society for Cardiovascular Angiography and Interventions definition for periprocedural MI will also be recorded.

The 4th Universal Definition of PCI related MI defines:

- Participants with normal baseline cardiac biomarkers
  - Cardiac troponin (cTN) >5x the 99^th^ percentile of upper reference limit (URL)
- Participants with elevated baseline cardiac biomarkers
  - Rise in post procedure cTN by >20% and be at least >5x 99^th^ percentile of URL AND
  - At least one of the following
    - New ischaemic ECG changes
    - Development of new pathological Q waves
    - Imaging evidence of new loss of viable myocardium or new regional wall motion abnormality in a pattern consistent with an ischaemic aetiology
    - Angiographic findings consistent with a procedural flow limiting complication such as coronary dissection, occlusion of a major epicardial artery or a side branch occlusion/thrombus, disruption or collateral flow or distal embolisation

The Society for Cardiovascular Angiography and Interventions definition for periprocedural MI defines:

- Participants with normal baseline cardiac biomarkers
  - CK-MB >10x upper limit normal (ULN) or cTn (I or T) >70x ULN, or
  - CK-MB >5x ULN or cTn >35x ULN plus new Q-waves in >2 contiguous leads or LBBB
- Participants with elevated baseline cardiac biomarkers
  - Baseline biomarkers are stable or falling:
    - CK-MB >10x ULN or cTn (I or T) >70x ULN of **most recent pre-procedure level**, or
    - CK-MB >5x ULN or cTn >35x ULN of **most recent pre-procedure level** plus new Q-waves in >2 contiguous leads or LBBB

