# Data Management, Statistical Analysis and Record Keeping

## **Statistical Methods**

This is a double-arm, open-label, randomized controlled trial of the CorPath GRX System designed to evaluate the safety and effectiveness of the clinical and technical performance of the CorPath GRX System in the delivery and manipulation of coronary guidewires and stent/balloon catheters, and remote manipulation of guide catheters for use in PCI in comparison to standard of care. The analysis of data collected as part of the RCT will include, but may not be limited to, the Objectives and Measures outlined in Section 3.0 of this protocol. Continuous variables will be summarized using the number of observations, mean, standard deviation, median, min and max values. Categorical variables will be summarized with the number and percent in each category out of the number observed. Two-sided 95% confidence intervals may be calculated and two-sided p-values < 0.05 will be considered statistically significant.

The outcome of patient radiation exposure will be analysed using variance (ANOVA). As each participant may have multiple lesions, the outcome of clinical success at day 3 will be analysed using a two level multilevel models. Logit link will be used with a binomial distribution and restricted maximum likelihood (REML) will be used for estimation. Predictor variables in the models will include treatment group.

Technical success will analysed with Fisher’s exact test, comparing the proportion of participants with technical success between the two groups. Logistic regression will be used to compare technical success accounting for lesion complexity. For all other secondary outcomes, continuous outcomes will be measured using independent t-test (or non-parametric alternative depending on distributional assumptions), and categorical outcomes analysed by Fisher’s exact test. For outcomes measured repeatedly over time, multilevel models with an appropriate link functions will be used for analysis.

All statistical analyses will be performed using SAS software (version 9.4) or other widely accepted statistical or graphical software.

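### The multilevel rule for repeated outcomes takes in MACE; coded cumulatively by visit with visit terms, its odds ratio is arbitrary, and Section 8.1 should name an event-date analysis instead

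*Protocol*

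**What the plan says.** Two adjacent rules in Section 8.1 (Statistical Methods) can claim MACE. For the remaining secondary outcomes, the protocol wants "categorical outcomes analysed by Fisher’s exact test". The next sentence reads: "For outcomes measured repeatedly over time, multilevel models with an appropriate link functions will be used for analysis".

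Section 2.4.1 says "MACE will be measured at each visit of the study", and the Summary lists the time points: "MACE that occurs within 72 hours of the procedure or prior to hospital discharge, whichever occurs first, day 30 and 1 year". Section 7.7.2 (Event Assessments) makes MACE a composite of cardiac death, myocardial infarction and clinically driven target vessel revascularisation, and counts a death of undetermined cause as cardiac.

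The protocol does not name MACE under either rule. It does not say whether MACE at a visit means any event since the procedure or a new event since the last visit, and the only model predictor it names is treatment group. For the clinical-success model it says "Logit link will be used with a binomial distribution and restricted maximum likelihood (REML) will be used for estimation"; this is not expressly carried over to the repeated outcomes. No time-to-event method is named.

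**The concern.** A multilevel model for a yes/no outcome over visits suits a state that can come and go, such as a symptom. MACE by a given visit cannot go back to no, and one of its components ends follow-up. A participant effect then has to explain an almost deterministic dependence between visits, and the odds ratio is conditional on that effect.

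MACE is one of the two safety measures in Section 2.4, and the one that is adjudicated and followed to 1 year. If the named method were applied to it in the most natural coding, the reported treatment effect would depend on where the software stopped. If another coding were chosen, the result would differ greatly on the same data. The protocol also leaves open whether Fisher's test or the model is the analysis, in a trial that Section 8.1 calls open-label.

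**Working it through.** **The plan's own figure.** The protocol gives no design figure for MACE. Its one power statement concerns radiation: difference 0.20 × 1284 = 256.8 mGy, SD √[(180² + 142.83²)/2] = 162.5, 150 per arm, two-sided 5%. Power is about 100%, so the stated figure of more than 99% reproduces. It has no bearing on MACE.

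**Inputs.** 150 per arm and three time points come from the protocol. Event counts are assumed, because the protocol gives no MACE rate. First events by 72 h/discharge, between then and day 30, and between day 30 and 1 year:
- Low: control 4, 3, 8 (15 in all); robotic 3, 2, 5 (10 in all).
- High: control 9, 5, 10 (24 in all); robotic 6, 3, 7 (16 in all).

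**Benchmark.** Plain cumulative odds ratios, robotic versus control, at the three time points:
- Low: (3/147)/(4/146) = 0.74; (5/145)/(7/143) = 0.70; (10/140)/(15/135) = 0.64.
- High: (6/144)/(9/141) = 0.65; (9/141)/(14/136) = 0.62; (16/134)/(24/126) = 0.63.

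**Model.** logit P(Yᵢⱼ = 1 | uᵢ) = αⱼ + β·armᵢ + uᵢ, with uᵢ normal with mean 0 and SD σ. The log-likelihood was maximised over α and β at each fixed σ by numerical integration.

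**(a) Cumulative coding with visit terms.** Only the patterns 000, 001, 011 and 111 can occur. Any finite σ puts some probability on impossible patterns such as 010. Raising σ, with α and β in proportion, takes that probability away.

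| σ | Low: log-lik. | log OR | OR | log OR/σ | High: log-lik. | log OR | OR | log OR/σ |
|---|---|---|---|---|---|---|---|---|
| 0.01 | −168.88 | −0.392 | 0.68 | – | −256.68 | −0.462 | 0.63 | – |
| 4 | −117.49 | −0.905 | 0.40 | −0.226 | −170.68 | −1.091 | 0.34 | −0.273 |
| 16 | −111.15 | −3.315 | 0.036 | −0.207 | −159.36 | −3.902 | 0.020 | −0.244 |
| 32 | −111.014 | −6.594 | 0.0014 | −0.206 | −159.040 | −7.744 | 0.00043 | −0.242 |
| 64 | −111.012 | −13.172 | 0.0000019 | −0.206 | −159.033 | −15.469 | 0.00000019 | −0.242 |

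The log-likelihood rises at every σ tried and flattens without turning. The ratio log OR/σ settles, so only that ratio is identified and the odds ratio itself is arbitrary. A REML pseudo-likelihood fit did not converge in 300 iterations: the variance sat at the search bound and the treatment coefficient swung in sign and size.

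**(b) Cumulative coding without visit terms.** A very large σ would allow only 000 and 111, which the data contradict, so σ stays finite. Of the values tried, the likelihood is highest at σ = 4 (low, OR 0.42) and σ = 6 (high, OR 0.23). Both are far more extreme than any per-visit odds ratio above.

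**(c) New event per interval with visit terms.** Coded 1 in the interval of the first event and 0 in the others, with all participants kept throughout. The likelihood is highest at the smallest σ: low −111.65 at 0.01 against −112.54 at 1; high −160.90 against −163.07. The odds ratios are 0.66 and 0.65, and the REML fit converges to the same values with variance about 0.00005. The fit is usable, but the multilevel part does nothing.

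**The case against.** The strongest reply is that the protocol does not compel the failing model. MACE is never named under the multilevel rule, the link is left open, and the Fisher sentence gives the per-visit 2×2 comparison used above as the benchmark. The rule has other targets: cost at day 30 and 1 year, health-care resource use, vital signs and laboratory tests. Divergence needs cumulative coding and visit terms together, and neither is fixed. Even then the arm contrast is identified up to scale, and a variance at its bound would be noticed. Coding, censoring and competing events are often left to an analysis plan, and one may exist.

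Most of this stands, and it limits the point. It does not remove it. The protocol has gone beyond leaving the matter open: it names a method whose wording reaches MACE, next to a second rule that also reaches it, and the first does not suit a cumulative composite with a fatal component.

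A reader might also infer three stronger things that the text does not support:
- That the rule drops deaths. With interval coding a cardiac death counts in its own interval; with cumulative coding it stays a yes. The sentence "Categorical variables will be summarized with the number and percent in each category out of the number observed" governs descriptive summaries and not the model.
- That participants who withdraw early contribute nothing. A multilevel model uses every visit a participant has.
- That day-30 MACE covers widely varying exposure, because the visit has a ±5-day window (Sections 3.3 and 7.5) and a missed visit may be rescheduled (Section 6.2). Those rules schedule visits. Nothing says that an event is assigned to the visit at which it is reported.

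**Conclusion.** The point holds in conditional form. On its plain wording the multilevel sentence covers MACE, and it competes with the Fisher sentence. Coded cumulatively with visit terms, MACE gives a participant variance with no finite maximum and an odds ratio without meaning. Coded cumulatively without visit terms, it gives a finite but exaggerated odds ratio. Coded as new events per interval, it gives a usable one. On the same assumed low-scenario data, one sentence can thus yield 0.66, 0.42 or a value approaching zero.

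It would be wrong to read this as saying that the trial's MACE analysis must fail, or to quote any one extreme odds ratio as its size, since such a figure only reflects where the search stops. The divergence follows from the four possible patterns and does not depend on the assumed event counts; the other estimates do depend on them. The cumulative reading is the natural one of the Summary's time points but is not stated. The correction should be made; it does not touch the radiation comparison on which the sample size rests.

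**What to change.** In Section 8.1, exempt MACE from the multilevel sentence, keep that sentence for outcomes that are truly repeated, and say that the MACE analysis below replaces Fisher's test. Then specify:
- Outcome: time from the start of the index procedure to first adjudicated MACE, by event date. MACE at 30 days and at 1 year means an event dated on or before day 30 or day 365.
- Estimates: cumulative risk per arm at 30 and 365 days, with the between-arm difference and 95% CI.
- Test: log-rank test or Cox model.
- Follow-up: censor at last contact; treat non-cardiac death as a competing event, since only cardiac and undetermined deaths count as MACE.

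The cost is one paragraph and slightly more analysis work. MACE is already reported from visit 2 to visit 5 (Section 7.7.2), on a separate form per event (Section 7.8.1), and adjudicated from source data (Section 10.2). The protocol does not list the form's fields; I assume that the event date is on it or in the source documents. No new participants, visits or procedures are needed.

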## **Data Management**

The site will maintain appropriate medical and research records for this trial, in compliance with regulatory and institutional requirements for the protection of confidentiality of participants. Source data are all information, original records of clinical findings, observations, or other activities in a study necessary for the reconstruction and evaluation of the trial.

## **Study Data Requirements**

To ensure data quality and completeness, all required data will be recorded on standardized electronic case report forms (eCRFs). eCRFs must be completed for each participant and once complete signed by the Investigator. The Investigator, or their authorized designee, is responsible for recording all study data in the eCRFs.

## **Data Entry**

Authorized study personnel will enter data directly into the eCRF. During data entry, each field is automatically subjected to data type verification and range checking. If an error occurs, the system ensures that the error is addressed before moving to the next entry field.

## **Final Data Analyses**

All datasets for analyses will undergo a final data cleaning procedure unique to each exported dataset.

## **Data Retention**

Data will be stored, accessed, archived and destroyed as per NSW Health Policies and the NHMRC National Statement on Ethical Conduct in Human Research. See section 9 for data protection. Study documents should be retained for a minimum of 15 years after the completion of the study (or greater according to site specific requirements). No records will be destroyed without the written consent of the Sponsor.

# Monitoring

## **Protocol Training**

Training on study protocol requirements will be provided for the entire study team at the initiation of the study. It is ultimately the responsibility of the Investigator to ensure all clinical site personnel participating in this study are adequately trained.

To ensure uniform data collection and protocol compliance, the study initiation visits to review the clinical protocol, techniques for the identification of eligible participants, instructions on in-hospital data collection, methods for soliciting data from alternative sources, and schedule for follow-up with study site personnel.

## **Device Training**

The Robotic PCI will only be performed by qualified investigators familiar with the CorPath^®^ GRX System. Training on the CorPath^®^ GRX System and procedure will be performed and documented for the site Investigator who is responsible for using the device.

## **Confidentiality and Protection of Study Files**

All data collection and reporting will follow strict adherence to Australian Privacy Legislation and NSW Health Policies for participant confidentiality.

All participants medical and procedural information will be kept on a password protected computer on an NSW Health Departmental password accessed network drive within a locked office. Once enrolled in the trial, participants will be allocated a unique identifier number. All documents containing identifiable information will also be password protected. It is important for participants to be re-identifiable for the purpose of reviewing medical records and any documents containing this information will only be accessible by study team. The re-identifiable/coded (it is possible to use the code to re-identify you) information held by the study team however will not be destroyed.

Any breaches in confidentiality will be reported in accordance with these policies.

# Data Quality Assurance

## **Clinical Event Handling**

This RCT will collect data on participants undergoing standard treatments and procedures. Investigators will be asked to provide documentation of events on the eCRFs related to specific procedural events and device complications. The site will follow their routine hospital procedures for adverse event handling, as necessary.

## **Study Endpoint Event Adjudication**

An independent events committee will review all clinical events associated with the study endpoints. Adjudication will be based on narratives and source data supplied by the sites. Source data that may be collected for review include, but are not limited to, de-identified angiograms (diagnostic and procedural), catheterization lab report, procedure report, discharge summary, lab reports, and pre- and post-procedure ECGs. The site may be contacted for queries and additional support documentation.

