## **Strategy for Recruitment and Retention**

All participants who are presenting to Liverpool Hospital for angiography and potential PCI will be asked to participate in this study. Participants will be consented according to Section 11.2 of the protocol.

After the participant has provided consent, the Investigator will confirm eligibility against the inclusion and exclusion criteria. If the participant meets the criteria they will be randomized according to Section 5.3 of the protocol. The participant and their significant others will be blinded to the method of PCI.

Participants will be asked to return for study visits as identified in Section 7. The participant will be contacted prior to the visit to confirm the appointment. If they are unable to attend all efforts will be made to collect the measurements as per the protocol.

If participants withdraws from the study please refer to Section 6.

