## **Randomisation**

Participants will be randomized 1:1 to the PCI performed using standard care or technology-assisted PCI in blocks to ensure balanced distribution of the treatment groups at all times. The study team will enter the participant screening information into the electronic data capture (EDC) system after informed consent has been obtained. Once the participant is determined to be eligible prior to the Index Procedure the study team will randomise the participant using the EDC. The Investigator will be advised of this and the allocated method of PCI will be performed. The participant will ideally remain blinded to the method of PCI performed.

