  - Baseline biomarkers have not been shown to be stable or falling: CK-MB (or cTn) rises by an absolute increment equal to those recommended above plus new ST-segment elevation or depression plus signs consistent with a clinically relevant MI, such as new onset or worsening heart failure or sustained hypotension.

**Target Vessel Revascularization (TVR):** Ischemia-driven repeat percutaneous intervention of the target vessel or bypass surgery of the target vessel. A TVR will be considered as ischemia-driven if the target vessel diameter stenosis is
[figure not shown]
≥50% and any of the following are present:

- A positive functional study corresponding to the area served by the target vessel.
- Ischemic ECG changes at rest in a distribution consistent with the target vessel.
- Ischemic symptoms referable to the target lesion.

**In-Hospital MACE:** MACE that occurs within 72 hours of the procedure or prior to hospital discharge, whichever occurs first, in a participant treated with the CorPath GRX System.

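### Section 10.2 makes the events committee independent but not masked, leaving the judgement-based parts of MACE open to detection bias in an open-label trial

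*Protocol*

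**What the plan says.** Section 8.1 (Statistical Methods) describes the design: "This is a double-arm, open-label, randomized controlled trial of the CorPath GRX System". Blinding is mentioned in two other places, and both concern the participant side. Strategy for Recruitment and Retention says "The participant and their significant others will be blinded to the method of PCI", and Section 5.3 (Randomisation) softens this: "The participant will ideally remain blinded to the method of PCI performed".

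For MACE, Section 7.7.2 says "Event Assessments will be reviewed by the End-Point Adjudication Committee". Section 10.2 adds "An independent events committee will review all clinical events associated with the study endpoints" and gives the evidence base: "Adjudication will be based on narratives and source data supplied by the sites". It then lists, as an optional and open-ended set, source data that may be gathered: "de-identified angiograms (diagnostic and procedural), catheterization lab report, procedure report, discharge summary, lab reports, and pre- and post-procedure ECGs". It also allows the site to be contacted with queries.

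MACE is a safety measure at every visit (Section 2.4.1). Its in-hospital form is part of the definition of clinical success (Section 2.2.1).

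**The concern.** Independence and masking are different safeguards. Independence means that adjudicators have no stake in the site's classification. Masking means that they do not know which technique was used. Section 10.2 provides the first and is silent on the second, while drawing its material from sites that know the allocation.

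At stake is the comparison of MACE between arms, and through in-hospital MACE the comparison of clinical success. An adjudicator who knows that a case was robotic may read an ambiguous death, angiogram or repeat procedure differently from one who does not. Central adjudication is the main check that the protocol describes on classification by unblinded sites. If the committee sees the arm, much of that check's value against detection bias is lost.

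**Working it through.** No stated figure of the protocol bears on this point. Its one sizing calculation (Section 8.1) concerns patient radiation. The difference is 0.20 × 1284 = 256.8 mGy, the pooled SD is √((180² + 142.83²)/2) = 162.48, and with 150 per arm power is about 1.00, which agrees with the stated figure of above 99%. That outcome is an instrument reading and is not adjudicated. The check is therefore a reading of the text.

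**1. Who is masked?** Participants and their significant others, with the qualifier in 5.3. No section says that outcome assessors or the events committee are.

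**2. What does the committee receive?** Narratives and source data from the sites. The catheterisation-lab report, procedure report and discharge summary are named as possible items. No step removes the technique. The de-identification wording stands before the angiograms; even if it were stretched over the whole list, it would remove the patient's identity and not the arm.

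**3. Would those papers show the arm?** The protocol does not say so. However, Section 7.2.3 requires a record of robotic stent measurement, use of robotic navigation algorithms and any need for manual input. Section 7.2.6 requires the reason for conversion to manual, and Section 7.2.7 requires any partial robotic assistance. An unredacted account of the procedure would ordinarily carry some of this.

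**4. Which MACE components need judgement, and what limits it (Section 7.7.2)?**

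| Component | Where judgement enters | What limits it |
|---|---|---|
| Cardiac death | Attribution of cause | A death whose cause cannot be determined counts as cardiac |
| MI | Angiographic findings suggesting a flow-limiting complication, one of four supporting criteria | Troponin must exceed 5 times the 99th percentile |
| Target vessel revascularisation | "Ischemic symptoms referable to the target lesion", one of three alternative criteria | Target vessel stenosis of at least 50% is needed as well |

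Judgement remains in each row, within bounds.

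**5. Can the definitions be applied by a masked committee?** Not all of them. Section 7.7.2 and Appendix A confine in-hospital MACE to participants treated with the robotic system, so applying the definition literally requires knowing the treatment received.

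**6. How large could the effect be?** The protocol gives no MACE rate. Purely as an assumption, take equal true rates of 3% to 10% in both arms, so 0.03 × 150 = 4.5 to 0.10 × 150 = 15 events per arm. If a fraction *m* of events in one arm were under-called, the apparent risk ratio would be 1 − *m*. For *m* of 10% to 30% that is 0.9 to 0.7 with no true difference, a shift of 4.5 × 0.10 = 0.45 to 15 × 0.30 = 4.5 events. Both the rates and *m* are assumed. The range shows that a few calls can matter when events are sparse; it does not estimate the bias in this trial.

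**The case against.** The strongest reply is that the protocol is silent rather than wrong. The source list in 10.2 is permissive and open-ended: it neither demands unredacted reports nor rules out masking, and a committee charter that is not shown might require it. This stands in part. A reader might infer that 10.2 fixes the evidence as unmasked reports, or that the adjudicators do know the arm; the text supports neither statement. But the protocol does set out who is blinded and what the committee works from, the use of site narratives is not conditional, and no charter is referred to. Anyone following 10.2 as written has no instruction to withhold the arm.

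A second reply is that the definitions already constrain judgement, and that participant blinding, where it holds, gives some protection to symptom reporting. This also stands, so it would be too strong to call the committee the only protection. The limits narrow the exposure without closing it.

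Third, the only powered outcome is radiation exposure, which needs no adjudication. That is correct and keeps the point in proportion. MACE still carries the safety comparison.

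Finally, redaction could strip clinical evidence. Section 7.2.6 lists a condition needing rapid medical intervention as a ground for conversion, so deleting all conversion text could hide the event itself. This is a sound warning and shapes the fix.

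**Conclusion.** The point holds as a cheap improvement to the design. Section 10.2 provides independence without masking, and the material that it names would ordinarily reveal the technique. Cause of death, angiographic support for MI and ischaemia-driven revascularisation are therefore open to detection bias, within the limits set by the objective thresholds. This rests on one strong inference, that unredacted procedure documents and narratives identify robotic cases, and on there being no masking rule in a document outside the protocol.

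The size of the bias cannot be stated. A reader might be tempted to take the 97.6% clinical success in Section 1.3.2, compute 150 × 0.024 = 3.6 failures per arm, and treat one reclassified event as 1/3.6 = 28% of MACE. The documents do not support that. The 97.6% is a rate per treated lesion from another study. Clinical success also fails on residual stenosis, so not every failure is a MACE. And it covers only in-hospital events, not those at day 30 or one year. Nothing in the protocol shows that bias will occur, or in which direction.

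**What to change.** - In Section 10.2, state that the events committee is masked to allocation.
- Before submission, have existing trial staff redact robotic and manual wording and device names from narratives, catheterisation-lab reports, procedure reports and discharge summaries. Keep the clinical facts, including the clinical events that led to any conversion, in neutral terms. Treat answers to committee queries the same way.
- Log any case in which the committee becomes unmasked.
- Leave the judgement of device-relatedness with the investigator (Section 7.7.4), apart from event classification.
- Reword in-hospital MACE in Section 7.7.2 and Appendix A so that it applies to both arms and can be used without knowing the treatment.

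The cost is a paragraph in 10.2, a wording change in two places, and staff time to redact event packets. No new assessor, visit or procedure is needed. The remaining downside is occasional unmasking from the angiograms themselves, which the log would record.
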